#### Incentives

Learners in both groups receive incentives for participating. The incentives are intended to enhance motivation of the learners to use the mobile app and complete study questionnaires. The learners receive Amazon gift cards throughout the study valued at US $20 at baseline, $2.50 for each completed SBIRT usage questionnaire, and $20 at the end of the study for answering the final questionnaire. Maximum payment is US $65 plus participation in a US $50 gift card lottery based on the completion of the SBIRT usage questionnaires.

#### Measures

Data on participants include demographic characteristics, training institution and level of training, type of patients served in clinical placement, and pre-post TPB-based questions to capture the TPB constructs described above (Table 1).

**Table 1 table1:** Measures used in the screening, brief intervention, and referral to treatment (SBIRT) mobile app randomized controlled trial (RCT).

Source	Data elements	Instrument	Timeline
All participants	Demographic characteristics	Self-report	Baseline
All participants	Type of clinical placement and population served	Self-report	Baseline
All participants	SBIRT^a^ attitudes, norms, behavioral control	TPB^b^-based survey (22 items)	Baseline and 10 weeks
All participants	Delivery of SBIRT components during clinical placement	Survey	Weekly
All participants	Satisfaction with the app and usability	SUS^c^ (10 items)	10 weeks
Control participants	Satisfaction with SBIRT	Survey (10 items)	10 weeks

^a^SBIRT: screening, brief intervention, and referral to treatment.

^b^TPB: theory of planned behavior.

^c^SUS: system usability scale.

### Pre-Post Assessment Questions

The team developed a 22-item questionnaire based on the TPB model. Likert-scaled items assess attitudes and beliefs including importance and efficacy of SBIRT, perceived patient willingness to participate in SBIRT, substance use epidemiology and clinical significance, and subjective norms and perceived behavioral control in the clinic setting. Three items assess confidence in the respondents’ ability to screen for alcohol or drug use problems, deliver a brief intervention, and to make referrals. One item assesses intent to perform SBIRT “whenever possible in my clinical/field placement.” All participants complete this questionnaire at baseline and again at 10 weeks. For intervention participants, baseline TPB responses are used to tailor their app experience by making specific recommendations of what the learner might need to review within the app’s library.

The system usability scale (SUS) [46] is a 10-item Likert scale instrument developed to measure aspects of usability including system complexity and need for support and training. It yields a single score ranging from 0 to 100. Intervention group participants complete this measure at follow-up.

### Satisfaction

We developed a 10-item Likert scale questionnaire to measure the experiences of control group participants, as a counterpart to the SUS. Items include barriers and challenges to SBIRT delivery to determine why some participants might not have used SBIRT in the context of their clinical placement. We included the satisfaction questionnaire for control participants only because we want to ensure they have an equivalent number of questions to the intervention participants, and we were concerned about survey burden with our intervention participants.

### Utilization.

At the end of each clinic week, every participant is sent (via email or text) a Qualtrics link asking them to report the total number of patients they have seen in the preceding week. Participants then are asked how many of those patients they screened for alcohol, drug, or tobacco use, how many they did a brief intervention with, and how many they either referred to a specialty substance use treatment clinic or discussed with their field supervisor.

### Intervention

#### Design and Function

The SBIRT app has the following three primary functions to address TPB concepts: (1) Review SBIRT skills (to help change beliefs and attitudes), (2) Apply SBIRT skills in clinic practice (to help impact attitudes, perceived behavioral control), and (3) Report SBIRT use (to report norms, as well as study outcomes). A fourth component, the Tools section, includes additional reference material and links (Figure 3). After downloading the app, intervention learners create an account and complete the pre-TPB survey. Immediate TPB results are given to the learners along with tailored recommendations on what they should do next. For example, if learners score low on SBIRT knowledge, they are directed to the Review section. A progress checklist in the Tools section reminds them of “homework” they still need to complete. Throughout the study intervention learners are reminded to use the app via the weekly SBIRT usage surveys and periodic text messages promoting app usage.

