**Methods:**

Intended for use after classroom training occurs, the mobile app has three primary functions designed to increase behavioral intent to deliver SBIRT: (1) review skills (ie, address knowledge and beliefs about SBIRT), (2) apply skills with patients (ie, build confidence and perceived behavioral control), and (3) report performance data (ie, increase accountability and social norms and/or influence). The app includes depression and anxiety screening tools due to high comorbidity with substance use. A randomized controlled trial (RCT) is in progress among health and social service learners (N=200) recruited from 3 universities and 6 different training programs in nursing, social work, internal medicine, psychiatry, and psychology. Participants are randomized to SBIRT classroom instruction alone or classroom instruction plus app access prior to beginning their field placement rotations. TPB-based data are collected via Qualtrics or via the mobile app pre-post and SBIRT utilization, weekly for 10 weeks. Key outcomes include the frequency of and self-reported confidence in delivery of SBIRT.

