#### Report

The Report section was originally conceptualized as a library of tools for instructors and clinical preceptors to track and evaluate their learners. We initially included a collection of pre-post surveys and weekly SBIRT usage items that intervention participants would complete. In order to standardize the data collection procedures across control and intervention participants, all weekly SBIRT usage surveys were completed via Qualtrics. Intervention participants still completed the pre-post TPB surveys and final satisfaction surveys on the app. However, instructors do not receive reports regarding use of the app or SBIRT by learners.

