#### Tools

The Tools section includes social networking, feedback and tracking, and gamification or incentive-building tools. Social networking tools include the “social connection” to send message questions to the study team or other app users. The “Progress Checklist” allows learners to check their progress on which pages they have visited and which pages they still need to review. “Technological Support” is included in this section for those who have technical difficulties and can contact the app developers directly for help. “Leaderboard” is a page on which other learners who are using the app are listed, along with a point system indicating frequency of app use. Leaderboard rankings were tied to lottery tickets and bonus incentives (Figure 4).

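### The weekly survey that measures SBIRT delivery also serves as an app reminder in the intervention arm only, and the lottery and maximum-payment statements need reconciling

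*Protocol article*

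**What the plan says.** **Outcome and instrument.** The abstract of the protocol article states: "Key outcomes include the frequency of and self-reported confidence in delivery of SBIRT". Delivery frequency comes from a weekly self-report. Under Utilization, "every participant is sent (via email or text) a Qualtrics link asking them to report the total number of patients they have seen", followed by how many of those patients were screened, given a brief intervention, or referred or discussed with a supervisor. Table 1 lists no other source for delivery.

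**Aim of a common channel.** The Report section explains why weekly reporting was taken out of the app: "In order to standardize the data collection procedures across control and intervention participants, all weekly SBIRT usage surveys were completed via Qualtrics".

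**Use of the survey as a reminder.** Design and Function says that, for the whole study, "intervention learners are reminded to use the app via the weekly SBIRT usage surveys", and names periodic promotional text messages as a second means. Controls have no app (Control Arm section), so this can apply to one arm only.

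**Payments and lottery.** The Incentives section, written for both groups, gives $20 at baseline, $2.50 per completed weekly survey and $20 at the end, and concludes: "Maximum payment is US $65 plus participation in a US $50 gift card lottery based on the completion of the SBIRT usage questionnaires". The Tools section describes a leaderboard that scores how often the app is used, and adds: "Leaderboard rankings were tied to lottery tickets and bonus incentives". The Intervention Arm section mentions modest incentives for app use. The Limitations section acknowledges them, on the ground that they would probably be absent from routine practice.

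**The concern.** Learners know whether they have the app, and they count their own SBIRT deliveries. If the message that asks for the count also urges app use in one arm, measurement and intervention are mixed at the moment of reporting. An intervention learner may be more inclined to answer, or may report more generously, because the message signals what the study hopes to see. A control learner receives no such signal. Either effect would add to or mask the app's real effect on delivery, and the data could not separate the two.

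The incentive text raises a second, mainly documentary problem. One section presents the lottery as a common reward for completing surveys. Another awards lottery tickets and bonuses for app use, which controls cannot earn. A reader cannot tell whether the arms have equal chances in the lottery, or what an intervention participant can receive at most.

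**Working it through.** **1. The stated maximum payment.** Inputs are from the Incentives section, with 10 weekly surveys from the abstract and Study Design.

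- Baseline: $20
- Weekly surveys: 10 × $2.50 = $25
- Final questionnaire: $20
- Sum: 20 + 25 + 20 = **$65**

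This reproduces the stated maximum exactly. The remainder for anything else is 65 − 65 = $0. A bonus with cash value would therefore take an intervention participant above the stated maximum.

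**2. The lottery rules side by side.**

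| Section | What earns lottery entry | Who can earn it |
|---|---|---|
| Incentives | Completing the weekly usage surveys | Both arms |
| Tools | Leaderboard rank, scored on frequency of app use | Intervention arm only |

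If there is one lottery, the arms have unequal chances under a rule presented as common. If there are two, the Incentives section leaves one out. The text does not say which.

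**3. What is the same and what differs in the weekly survey.**

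- Same in both arms: Qualtrics channel, weekly timing, questions on patients seen and SBIRT components, and $2.50 per survey.
- Different: in the intervention arm the survey is also used to prompt app use.

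The difference lies in the context of the measurement, not in its items or its payment.

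**4. How a reporting shift would act (illustration only).** The documents give no size for any shift, so a range is shown. Assumptions: no true effect, two-sided alpha 0.05, outcome in standard deviation (SD) units, and n per arm of 100 (N=200 allocated 1:1) or 80 (assumed losses). With SE = √(2/n) and s = shift/SE, the chance of a significant result is 1 − Φ(1.96 − s) + Φ(−1.96 − s).

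| Shift in one arm (SD) | n = 100 per arm | n = 80 per arm |
|---|---|---|
| 0 | 0.050 | 0.050 |
| 0.05 | 0.064 | 0.062 |
| 0.1 | 0.109 | 0.097 |
| 0.2 | 0.293 | 0.244 |
| 0.3 | 0.564 | 0.475 |

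A shift of 0.05 SD hardly matters. A shift of 0.2 SD raises the false-positive chance well above 0.05.

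**5. Missed weeks.** Suppose a learner sees p patients a week, delivers SBIRT to d of them, and reports k weeks. The summed count is k·d, which rises with k. The rate per patient seen is k·d/(k·p) = d/p, which does not depend on k. Unequal response alone therefore distorts a summed count but not this rate. The rate is still exposed if the weeks reported are a selected set, or if the reported counts themselves shift.

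**The case against.** The strongest reply is that the documents describe the same reporting in both arms: same link, questions, timing and payment. That stands. A reader might infer from the reminder that outcome reporting does differ by arm, but the text supports only a risk of this.

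Second, no separate intervention version of the survey is described. The reminder could be added wording, or merely the cue of receiving a survey about SBIRT. A prompt also acts largely on the following week's behaviour, which is an intended effect of the intervention. This is fair as far as it goes. However, Design and Function lists the surveys beside promotional text messages as a means of reminding intervention learners, so the dual use is stated. Only its exact content is open.

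Third, leaderboard tickets reward app use, not survey completion, so they give no direct reason to answer more surveys. This stands: the lottery point is about consistent rules and bears on reporting only indirectly. It is also tempting to say that the two payment rules cannot both be followed. That holds only if there is a single lottery and the bonuses have cash value, and neither is stated.

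Fourth, one might translate an assumed gain in response into a percentage difference in delivery. That would need response rates the article does not give, and counts summed with missed weeks taken as zero. The Analyses section compares the rate of delivery, and the survey collects patients seen as a denominator, so no such figure is supported.

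Finally, the Limitations section discloses the app-use incentives. It does so as a matter of applicability to practice and does not address measurement of the outcome.

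**Conclusion.** The point holds as a risk and as a need to reconcile text. Using the outcome survey as an app reminder in one arm works against the article's own standardisation aim. In an unblinded trial with a self-reported outcome, it leaves room for response or reporting to differ for reasons other than SBIRT delivery. The size is unknown; the table above shows only what assumed shifts would do.

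The lottery has two stated bases, one of them open to the intervention arm alone. The $65 maximum is arithmetically correct for the listed payments but leaves nothing for a cash bonus. Whether it is actually exceeded depends on what the bonuses are, which the article does not say. The change is worth making because it is cheap and removes an avoidable ambiguity, not because bias has been shown.

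**What to change.** - **Survey.** Send both arms an identical weekly invitation and survey with no app content. Put all app reminders in the separate text messages that intervention learners already receive, and say in Design and Function what the weekly message contains.
- **Incentives.** Let the survey-completion lottery follow one rule in both arms. Keep any app-use reward separate, state what it is, and restate the maximum payment for the intervention arm. Bring the Incentives, Tools and Intervention Arm sections into agreement.
- **Analysis.** Compare weekly survey response by arm. Define the delivery rate per patient seen in reported weeks, so that a missed week does not count as zero delivery.

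**Cost.** The in-survey reminder is lost, though the text reminders remain. The invitation and incentive text must be edited, with notice to the review boards at the 3 sites. Enrolment began in September 2016 and is described as ongoing, so participants enrolled before the change will have had the earlier procedure. Record the date of the change so that the two periods can be told apart. If follow-up has already ended, the response comparison, the per-patient analysis and the correction of the incentive text can still be done.

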**Figure 3 figure3:**
[figure not shown]
Screen shot of the screening, brief intervention, and referral to treatment (SBIRT) mobile app home screen.

#### Review

The Review section includes content taught in the classroom (which is also available to learners online), as well as additional material. Subheadings include “Basics” (eg, epidemiology, drugs of abuse, consequences, defining SBIRT), “Screening” (eg, screening questions, sample scripts, and the Diagnostic and Statistical Manual of Mental Disorders, Fifth Edition [DSM-5] definition of substance use disorder [47]), “Brief Intervention” (eg, brief advice, motivational interviewing, harm reduction), “Referral to Treatment” (eg, referral processes, pharmacotherapy), and “Key Resources” (eg, case illustrations, video demonstrations, external links to the National Institute on Alcohol Abuse and Alcoholism, and the National Institute on Drug Abuse).

#### Apply

The Apply section assists learners in using SBIRT while with a patient in clinic placements. This section includes screener instruments, scoring tools, scripts, and step-by-step guidance for delivering a brief intervention or referring a patient to alcohol or drug treatment. For example, the app allows users to specify what they want to screen (eg, alcohol, drugs, depression, anxiety), tailors those questions by gender and age group (18 to 64 versus 65 and up), includes single-question hazardous drinking and drug use screeners, as well as the Alcohol Use Disorders Identification Test (AUDIT) [48], CRAFFT (CRAFFT is a mnemonic acronym of first letters of key words in six screening questions) [49], and Drug Abuse Screening Test (DAST) [50]. Depression screening using the Patient Health Questionnaire (PHQ-2 and PHQ-9) [51] and anxiety screening using the Generalized Anxiety Disorder (GAD-2 and GAD-7) [52] measures are also included due to high comorbidity with substance use and commonalities in intervention approaches. Other subsections include tips for delivering brief interventions, including brief negotiated interviews/motivational interviewing, and suggestions for making referrals (eg, referral processes, lists of local treatment resources, and national treatment locators).

#### Report

The Report section was originally conceptualized as a library of tools for instructors and clinical preceptors to track and evaluate their learners. We initially included a collection of pre-post surveys and weekly SBIRT usage items that intervention participants would complete. In order to standardize the data collection procedures across control and intervention participants, all weekly SBIRT usage surveys were completed via Qualtrics. Intervention participants still completed the pre-post TPB surveys and final satisfaction surveys on the app. However, instructors do not receive reports regarding use of the app or SBIRT by learners.

#### Tools

The Tools section includes social networking, feedback and tracking, and gamification or incentive-building tools. Social networking tools include the “social connection” to send message questions to the study team or other app users. The “Progress Checklist” allows learners to check their progress on which pages they have visited and which pages they still need to review. “Technological Support” is included in this section for those who have technical difficulties and can contact the app developers directly for help. “Leaderboard” is a page on which other learners who are using the app are listed, along with a point system indicating frequency of app use. Leaderboard rankings were tied to lottery tickets and bonus incentives (Figure 4).

**Figure 4 figure4:**
[figure not shown]
Screenshots of the Review, Apply, Report, and Tools subsections of the screening, brief intervention, and referral to treatment (SBIRT) mobile app.

### Analyses

Analyses will be conducted using SAS (SAS Institute Inc., 2011). Descriptive statistics, including distributions, means, standard deviations, skewness, and kurtosis will be obtained for all variables. Continuous measures will be tested for normality and homogeneity of variance. If the distribution is normal, Likert-scale responses will be analyzed as continuous scores [53]. Chi-square tests, student *t* tests, and analysis of variance (ANOVA) tests will be used to determine inclusion in multivariate regression models. Bivariate analyses will examine rate of SBIRT delivery in the two arms and comparison of TPB-based measures (eg, beliefs about SBIRT, social norms and influence, and perceived behavioral control). Multivariate analyses (logistic and multiple regression) will examine the impact of these factors on SBIRT delivery.

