#### Setting

The trial is being carried out at 3 sites, among 6 training programs: San Francisco State University (Social Work and Nursing), University of California, San Francisco (Internal Medicine and Psychiatry), and University of San Francisco (Nursing and Psychology). Institutional review boards at the 3 sites approved all study procedures. The study is not registered with ClinicalTrials.gov because the design does not include a collection of clinical data or patient-level outcomes.

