#### Participants

Study participants (trainees, N=200) are adult health professional learners in one of the designated training programs. Participants must have had prior classroom or online training in SBIRT within the past year and may not have previously used an SBIRT app. For learners who have not yet completed classroom-based SBIRT instruction, they are required to complete the following 3 online training modules developed by the research team: (1) Introduction to SBIRT, (2) Screening, and (3) Brief Intervention. The learner must be enrolled in a field placement and is required to have a mobile device to be in the study (Android or iOS). Field placements include a range of private and public healthcare and social service agencies in the San Francisco Bay Area.

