#### Recruitment and Randomization

Project faculty identified SBIRT educators at the participating training programs and received permission to recruit students. Students are recruited during scheduled classroom time using a detailed information sheet that specifies expectations, timing, and types of data to be collected. Absent learners are invited to participate via email recruitment. Participants provide informed consent to participate either live in classroom settings or via email.

Standard randomization procedures used in behavioral intervention studies are followed [45] using a variable block size with a 1:1 allocation to the intervention or control arm design. These procedures are carried out by the study project manager. Learners are assigned an identification number that is used for the randomization. A Web-based randomization tool is used to generate group assignments. Randomization is stratified by training program in order to have an even distribution of learners in the intervention and control groups from each program.

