This theory-based mobile app serves as a reference guide, a clinical tool, and a data collection instrument. Learners are expected to complete the initial TPB assessment questions before starting their clinical rotations and are then asked to use the app as often as possible during the course of providing direct care. The reporting function frequency of completion is dependent on the structure of the clinical rotation and the needs of the training program and/or preceptors. Although learners’ use of SBIRT is ultimately limited by what their clinical rotation and preceptor allows, this tool may increase the likelihood of effective SBIRT delivery in healthcare and social service settings. This initial presentation describes our mobile app development process, beta testing, and randomized trial methods, which aim to determine the potential impact of this digital tool.

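### Randomization is stratified by training program, but the arm comparison leaves program out and the regression models admit it only through a significance screen

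*Protocol article*

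**What the plan says.** On design, the Setting section states: "The trial is being carried out at 3 sites, among 6 training programs". The programs span nursing, social work, internal medicine, psychiatry and psychology. Recruitment and Randomization states: "Randomization is stratified by training program in order to have an even distribution of learners in the intervention and control groups from each program". Allocation is blocked, "using a variable block size with a 1:1 allocation to the intervention or control arm design". The planned size is 200 learners (Participants).

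On analysis, the Analyses section says three things:

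- Chi-square, Student t and ANOVA "tests will be used to determine inclusion in multivariate regression models". It does not say whether candidates are tested against outcome or against arm, and it lists no candidates.
- "Bivariate analyses will examine rate of SBIRT delivery in the two arms and comparison of TPB-based measures". No adjustment is named.
- Logistic and multiple regression then relate these factors to delivery. Neither arm nor training program is named as a required term.

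No section keeps training program in an arm comparison regardless of a test result.

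**The concern.** Blocking within program makes the two arms nearly identical in program mix. The difference between arms then no longer varies because of program. A two-sample test that ignores program still counts between-program variation as noise, so its standard error is larger than the true one. The estimate keeps the precision that stratification gave it, but the interval and test do not use it.

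The inclusion rule does not reliably repair this, because it makes a feature of the design depend on a p-value. It also leaves the reported model to be settled after the data are seen. In a logistic model it leaves open which odds ratio is being estimated, since the odds ratio with program in the model differs from the one without it.

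The article itself makes it plausible that program matters. Its Introduction cites studies in which delivery varied across health disciplines, although it gives no size.

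**Working it through.** **No figure to reproduce.** The article gives N=200 but no significance level, power, effect size, standard deviation or rate. What follows illustrates the size of the effect under stated assumptions.

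**Inputs from the article.** 200 learners, 1:1, so about 100 per arm; six strata; variable blocks.

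**Assumptions.** Two-sided 5% level; continuous outcome with within-arm SD 1; f is the share of outcome variance lying between programs, taken from 0 to 0.30. The true difference is the one that a conventional unadjusted calculation detects with 80% power:

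d = (1.960 + 0.842) × √(2/100) = 0.396 SD.

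**Formulas.**

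- Under stratified allocation the true variance of the difference is (1−f) × 2/100. The unadjusted test uses 2/100. Ratio of reported to true standard error = 1/√(1−f).
- Actual type I error of the unadjusted test = 2 × [1 − Φ(1.96/√(1−f))].
- Unadjusted power = Φ((d/√0.02 − 1.96)/√(1−f)), where d/√0.02 = 2.80.
- Adjusted power = Φ(2.80/√(1−f) − 1.96).

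Worked at f = 0.20, √0.80 = 0.894. The ratio is 1/0.894 = 1.118. Unadjusted power is Φ(0.84/0.894) = Φ(0.94) = 0.826. Adjusted power is Φ(3.13 − 1.96) = Φ(1.17) = 0.879.

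| f (assumed) | SE ratio | Actual type I error | Power, unadjusted | Power, adjusted | Loss (points) |
|---|---|---|---|---|---|
| 0 | 1.000 | 0.050 | 0.800 | 0.800 | 0 |
| 0.05 | 1.026 | 0.044 | 0.806 | 0.819 | 1.3 |
| 0.10 | 1.054 | 0.039 | 0.812 | 0.839 | 2.7 |
| 0.20 | 1.118 | 0.028 | 0.826 | 0.879 | 5.3 |
| 0.30 | 1.195 | 0.019 | 0.842 | 0.917 | 7.5 |

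**Simulation check.** 2,500 trials per setting, six strata of equal or unequal size, permuted blocks of 2, 4 and 6 (block sizes assumed). With program always in the model, type I error was 0.048 to 0.057 at every f. The unadjusted test fell to about 0.032 at f = 0.20 and 0.024 at f = 0.30, the same direction as the closed form and slightly less extreme.

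**What the screen would do with program (5% threshold assumed).**

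- Chi-square of program against arm: selected in 0% of simulated trials, at every f. The full loss remains.
- ANOVA of outcome on program: selected in about 65–69% of trials at f = 0.05, 96–97% at f = 0.10, and essentially 100% at f = 0.20 and above. Most of the loss is then recovered in the regression model.

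Under either reading the bivariate arm comparison stays unadjusted.

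**The case against.** The strongest reply is that this is a one-paragraph summary in a journal article, that forced stratum terms are commonly left to an analysis plan, and that the regression models read as explanatory work on the theory-of-planned-behavior factors rather than as the estimate of the arm effect. This stands in part. The article does not list the candidate variables, so it cannot be said that program is certain to be left out of the models. But the article does not merely omit a covariate list. It states a selection rule, and the only arm comparison it describes is bivariate. An analysis plan that forced program into every model would depart from that rule.

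A second reply is that an outcome-based screen would nearly always keep program whenever it explains much variance. That is correct. The larger losses in the table therefore belong to the bivariate comparison, or to a screen against arm, and not to an outcome-based screen.

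Third, the size is unknown. The article gives no between-program variance, and at f = 0 nothing is lost. The power loss also depends on the anchor. If 80% is taken as the power of the adjusted analysis instead, the unadjusted test has Φ(2.80 − 1.96 × 1.118) = 73% at f = 0.20 and Φ(2.80 − 1.96 × 1.195) = 68% at f = 0.30. The article states no power, so neither anchor is its own.

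Some stronger readings are not supported:

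- A reader might infer that selection by p-value inflates false positives. In the simulations, screening program in or out left type I error at or below about 5%, apart from simulation noise.
- A reader might equate the loss with a sample-size factor of 1/(1−f), for example 200/0.80 = 250. That matches interval width, not power, because the unadjusted estimate already has the smaller variance. With 80% power when adjusted, the unadjusted test at f = 0.20 needs about 200 × [(1.96 × 1.118 + 0.84)/2.80]² ≈ 234.
- A reader might take the remark in Principal Findings that "learners’ use of SBIRT is ultimately limited by what their clinical rotation and preceptor allows" as evidence about program. It concerns rotation and preceptor, so it is indirect at most.

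**Conclusion.** The concern holds as a mismatch between design and stated analysis. Randomization conditions on program, while the analysis ignores it in the bivariate comparison and makes it contingent in the models. For a continuous outcome the consequence is conservative inference: intervals too wide, type I error below nominal, and a power loss of about 1 to 3 points if program explains 5–10% of variance and about 5 to 8 points if it explains 20–30%. These figures rest on the assumed variance shares, about 100 learners per arm, and 80% power by the unadjusted calculation. They do not carry over to logistic models, where including or excluding program changes the odds ratio being estimated; that effect was not quantified. Nothing here indicates bias or excess false positives. It should be corrected because the correction is almost free and settles the model before outcomes are seen.

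**What to change.** In Analyses, replace the significance-based inclusion rule, for arm comparisons, with a prespecified model containing arm and training program (six levels) as a fixed term. Report that estimate as the main result for SBIRT delivery and for the theory-of-planned-behavior measures, with the unadjusted comparison as supportive. Name any further baseline covariate in advance, for example the baseline questionnaire score when the 10-week score is the outcome. Placement type or population served could be added only once its categories are defined, since the Measures table does not list them and their cost in degrees of freedom cannot be stated. For logistic models, say that the reported odds ratio is conditional on program.

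The cost is a change of wording and 6 − 1 = 5 degrees of freedom out of about 200. No new data are needed. The article describes recruitment as ongoing, so the change could be made before results are seen.
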